### Relevant concomitant care permitted or prohibited during the programme {11d}

Concomitant care is given according to local guidelines.

Repaglinide and midazolam are prohibited while the patient is receiving tecovirimat.

### Provisions for post-programme care {30}

After the patient’s final programme visit at D28, responsibility for clinical care is returned to the local healthcare system.

If a patient suffers harm as a result of their involvement in the programme, the Sponsor (the University of Oxford) has specialist insurance in place: Newline Underwriting Management Ltd, at Lloyd’s of London.

### Outcomes {12}

Treatment effects will be evaluated based on clinical, virological and safety outcomes described in Table 3.

**Table 3 pone.0278957.t003:** Outcome measures.

Assessment of…	Outcome measure
**Clinical outcomes**	Time to lesion(s) resolution, defined by: From a start point of date that treatment started. Until an endpoint of up to 14 days since treatment start. Where lesion resolution is the first day on which all lesions are resorbed, scabbed or desquamated and mucosal ulcers healed, and in the absence of any serious complications
	Clinical status defined by: Clinical status on day 14 and day 28 according to an ordinal scale assessed by a physician. The ordinal scale is a) no new or active lesions and no serious complications, b) active lesions and no serious complications, c) serious complication of monkeypox, d) death.
**Virological outcomes**	Virological status defined by Change from baseline in Monkeypox virus DNA levels in throat swabs on days 4, 8, 14 and 28. Change from baseline in Monkeypox virus DNA levels in blood on days 4, 8, 14 and 28. Presence of Monkeypox virus DNA in lesion swabs on days 4, 8, 14 and 28.
**Safety outcomes**	Number and type of Serious Adverse Events (SAEs), Suspected Adverse Reactions (SARS) and Suspected Unexpected Serious Adverse Reactions, (SUSARs) within 28 days of enrolment.

### Participant timeline {13}

The participant timeline is described in Fig 1.

**Fig 1 pone.0278957.g001:**
[figure not shown]
Schedule of enrolment, interventions and assessment. ^**a**^ The D21 visit will only be conducted for patients who test positive for monkeypox on D14 and remain hospitalised. ^**b**^ These tests will be voluntary. ^**c**^ Conducted +/- 24h of specified visit. ^**d**^ Two swabs taken per timepoint. Please see below for further details.

### Sample size {14}

This is an EAP with a primary objective of providing treatment to patients with monkeypox. A formal sample size has therefore not been calculated. Ethical approval has been obtained however for treating 100 patients.

### Recruitment {15}

An active monkeypox surveillance programme has been put in place to detect and report cases of monkeypox in the target Prefectures. The PI and Co-PI have conducted a community engagement programme to train all health personnel working at health facilities and strengthen capacity in the clinical diagnosis of monkeypox. Essential equipment has also been provided to health facilities across the Prefecture to assist with the diagnosis of monkeypox.

## Assignment of interventions: Allocation

### Sequence generation {16a}

This is not a clinical trial and patients are not randomised to treatment. All enrolled patients receive tecovirimat.

### Concealment mechanism {16b}

This is not a clinical trial and patients are not randomised to treatment. All enrolled patients receive tecovirimat.

### Implementation {16c}

This is not a clinical trial and patients are not randomised to treatment. All enrolled patients receive tecovirimat.

## Assignment of interventions: Blinding

### Who will be blinded {17a}

No one involved in the EAP is blinded to the intervention.

### Procedure for unblinding if needed {17b}

As the intervention is not blinded, there will no unblinding procedure.

## Data collection and management

### Plans for assessment and collection of outcomes {18a}

All data collected under the EAP are recorded on a paper CRF (**S1 Table**) by the PI or Co-PI and entered on to a RedCap database within 24 hours by the data manager who is also based at the district-level hospital.

All members of staff involved in the EAP have undergone training on the assessment of patient outcomes, including the differentiation between lesion types and reporting SAEs and SUSARs.

All blood, throat and lesion samples collected under this protocol are sent to the national reference laboratory at Institut Pasteur de Bangui for testing by G2R-G PCR assay–for the detection of MPXV (any clade)–and C3L PCR assay–for the detection of Clade I MPXV. The MPXV positive or negative result for each sample type are recorded on to the paper CRF and transferred on to the RedCap database.

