### Eligibility criteria {10}

#### Inclusion criteria

This programme is enrolling male and female patients who meet the following criteria:

Confirmation of monkeypox virus disease by PCR, or patients who are being managed as a presumptive case pending laboratory confirmation*Weight ≥13 kgWilling to provide informed consent to enrol in the programme

*A blood, pharyngeal, and lesion swab are taken for confirmation by qPCR positivity for monkeypox virus DNA, but enrolment will not await laboratory confirmation if there is high clinical suspicion of disease. A patient who is a presumptive case and subsequently tests negative for MPXV will exit the study. A positive PCR result on any of the samples constitutes evidence of MPXV infection.

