## Statistical methods

### Statistical methods for analysing outcomes {20a}

Clinical and virological outcomes will be assessed at D14 and D28 for all patients and then at D21 for patients who are still positive at D14. Due to the non-comparative nature of the study and small number of patients anticipated to be enrolled in the study, only descriptive analyses of clinical and virological outcomes will be presented in the final analysis; no inferential statistical testing will be performed to evaluate changes in outcomes.

To describe the cohort, patient demographics will be described in terms of the ratio of males to females in the cohort, and the median age and range in years. The number and percentage of patients with comorbidities at inclusion, including malaria and human immunodeficiency virus, infection will be presented, along with the median interval in days from symptom onset to initiation of treatment.

Signs and symptoms will be reported in terms of the number and percentage of patients presenting with the symptom, which are assessed at each visit and will be reported at baseline and post-baseline timepoint. Signs and symptoms will be reported for all patients both from a pre-defined list included in the CRF and any additional AEs that may have arisen from the point of consent until D28. The signs and symptom reporting will also include the number and percentage of patients with lesions–subcategorised in to active lesions, crusts and resolved lesions–their distribution and number of lesions observed.

Treatment adherence will be reported in terms of the number and percentage of patients who completed a full course of treatment. Non-adherence will be reported in a supplementary narrative explanation.

Patient outcomes will be reported as the number and percentage of participants who meet the clinical criteria described in Table 3 at D14 and D28, along with the number and percentage of participants who tested positive for mpox virus on D4, D8, D14, D21 and D28.

Narrative summaries of SAEs will be presented alongside a tabulated summary of the number and percentage of patients who experience each SAE, for which event names will be MedDRA coded. For each SAE the grade and outcome will be reported.

Full details of the planned analyses can be found in the Statistical Analysis Plan.

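### Throat and blood virological outcomes are defined as change in viral DNA level, but the protocol describes recording and reporting only positive or negative results

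*Protocol article*

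**What the plan says.** Three sections of the protocol article deal with virology.

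- **Outcomes {12}, Table 3.** The throat outcome is "Change from baseline in Monkeypox virus DNA levels in throat swabs on days 4, 8, 14 and 28". The blood outcome is "Change from baseline in Monkeypox virus DNA levels in blood on days 4, 8, 14 and 28". The lesion outcome is of a different kind: "Presence of Monkeypox virus DNA in lesion swabs on days 4, 8, 14 and 28".
- **Plans for assessment and collection of outcomes {18a}.** Specimens are tested with two PCR assays, both described by what they detect (the second is the "C3L PCR assay–for the detection of Clade I MPXV"). On data capture the section says: "The MPXV positive or negative result for each sample type are recorded on to the paper CRF", and from there it goes into RedCap. It names no cycle threshold (Ct), copy number or other measure of level.
- **Statistical methods for analysing outcomes {20a}.** The planned virological summary is "the number and percentage of participants who tested positive for mpox virus on D4, D8, D14, D21 and D28". No summary of DNA level, or of its change, is described.

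Two other places bear on the point. The footnote to the inclusion criteria calls the confirmatory test a qPCR. Confidentiality {27} says that electronic data are kept solely in RedCap.

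**The concern.** The outcome definition calls for a continuous measurement, while both the data capture and the analysis describe a binary one. If the programme is run as the article reads, the analyst will have no DNA level for throat or blood and cannot report two outcomes that the protocol names.

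Describing clinical, virological and safety outcomes is the secondary objective, and the only one that concerns data. The Background says that alternatives to mortality are needed as endpoints and that virological data on patients are lacking. The Discussion hopes that the results will help define outcome measures for later studies. How fast viral DNA falls in each compartment is information of that kind, and a positive/negative field loses most of it. Cases are sporadic and ethical approval covers 100 patients, so values that are not kept would be hard to replace.

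**Working it through.** The article gives no figure to reproduce. The check compares the data type that each section needs or supplies.

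| Component | Needed by Table 3 | Recorded under {18a} | Reported under {20a} | Derivable as described? |
|---|---|---|---|---|
| Throat | DNA level at baseline and D4, D8, D14, D28 | positive/negative | count and % positive | No |
| Blood | DNA level at baseline and D4, D8, D14, D28 | positive/negative | count and % positive | No |
| Lesion | presence of DNA at D4, D8, D14, D28 | positive/negative | count and % positive | Yes |

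**What a pair of binary results can show.** For one patient and one compartment, baseline and follow-up give four possible pairs.

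- Positive then positive: the level may have risen, stayed the same or fallen; the record cannot tell.
- Positive then negative: the level fell below detection, by an unknown amount.
- Negative then positive: the level rose above detection, by an unknown amount.
- Negative then negative: no measurable level at either time.

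None of these gives the size of a change, and the first does not even give its direction.

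**Extent.** Table 3 has 3 components × 4 visits = 12 outcome-by-visit combinations. Throat and blood account for 2 × 4 = 8 of them (8/12 = 67%). The other 4 are lesion outcomes, which the recorded data support.

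**Data needed.** Two compartments at 5 time points (baseline plus four visits) make 2 × 5 = 10 quantitative results per patient. At the approved ceiling of 100 patients that is at most 10 × 100 = 1,000 results, and fewer in practice because samples are taken only where possible.

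**Another route to the data?** Section {18a} says that all programme data go on the paper CRF and then into RedCap, and {27} names no other electronic store. The article describes no path by which a DNA level would reach the analyst.

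**The case against.** The strongest reply is that {18a} says a positive or negative result is recorded, not that nothing else is. The CRF (S1 Table) and the SAP are not at hand, and {20a} refers to the SAP for full detail. Either could contain a quantitative field or a summary of it. This stands as a limit: it is not shown that the values are absent. It does not remove the contradiction. The article is not silent on the data type; it states a binary one for both capture and analysis, and an SAP cannot recover a level that was never recorded. If the CRF does hold a level, {18a} and {20a} misdescribe the plan and still need correcting.

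A second reply is that nothing inferential rests on these outcomes. The primary objective is access to treatment, there is no sample-size calculation, and the analysis is descriptive. That stands, and it lowers the weight of the point.

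A reader might also infer more than the text supports:

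- **That all virological outcomes fail.** The lesion outcome matches the recorded data.
- **That the Clade I result is not captured.** The sentence on recording follows the description of both assays and can be read as covering both.
- **That percentages positive will overstate clearance, by counting patients who were never positive in blood or throat.** Under the inclusion criteria "A positive PCR result on any of the samples constitutes evidence of MPXV infection", so such patients can exist. But {20a} counts participants and plans no table by specimen, and Table 3 defines no clearance outcome. If positive means positive on any sample, every confirmed patient starts positive. The documents do not establish an inflated figure.
- **That Ct values are waiting in the laboratory.** The term qPCR makes this plausible, but nothing says that they are retained.

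**Conclusion.** The point holds for throat and blood. As described, two of the three virological components (8 of 12 outcome-by-visit combinations) cannot be derived, because the outcome is a change in level while the record and the planned summary are binary. This is a contradiction between stated sections, not detail left to the SAP.

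The conclusion assumes that {18a} and {20a} describe the virological data and summaries in full. If the CRF already carries a quantitative field, the problem shrinks to inaccurate wording in those two sections. The weight is moderate: the outcomes are secondary and descriptive, and no test or decision depends on them. It still deserves correction, because otherwise the programme cannot report part of its own secondary objective.

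**What to change.** Establish first whether the laboratory retains quantitative qPCR results, and then take one of two routes.

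1. **If it does.** Add to the CRF and RedCap the quantitative result (Ct or copies, one scale used throughout) and the limit of detection, for throat and blood at baseline and at each follow-up visit. Amend {18a} to say so. Add to {20a} a descriptive summary of change from baseline, separately for throat and blood, among patients positive in that compartment at baseline. Treat undetectable follow-up values as below the limit of detection and report how many there are at each visit.
2. **If it does not.** Restate the throat and blood outcomes in Table 3 as presence of DNA, as already done for lesion swabs.

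Either way, Table 3, {18a} and {20a} should end up describing the same measurement. While these sections are open, align the visits too: {20a} reports positivity at D21, which Table 3 does not list.

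The first route costs extra database fields, back-entry for patients already enrolled where values exist, and a few tables; it needs no new samples. The second costs only a wording change, but gives up the description of viral decline.

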### Plans to promote participant retention and complete follow-up {18b}

Patient outcomes in this programme are assessed at Days 14 and 28.

Patients who are enrolled in this programme will remain in hospital for a minimum of 14 days until the completion of treatment or, if patients are still positive for MPXV at Day 14, until they receive a negative PCR result and are clinically well to be discharged. All treatment will therefore be administered under the supervision of the PI or Co-PI.

Following discharge, patients will attend a final visit at Day 28.

### Data management {19}

Data are recorded on a paper CRF and then entered on to a RedCap database by the data manager based at the district-level hospital with other members of the study team.

The RedCap database contains data quality rules to prevent entry of erroneous data.

Centralised data monitoring is also implemented by the Sponsor to ensure completeness and accuracy of data relating to the primary and secondary outcome measures and patient safety.

The RedCap database will be held at the University of Oxford for a minimum of 25 years.

### Confidentiality {27}

All data and samples are labelled only with the patient’s anonymous subject ID code.

The consent form and enrolment log will remain at the site of enrolment during the study and then transferred to the Institut Pasteur de Bangui to be kept securely for a minimum of 3 years. This information will not be shared with any individual or organisation outside the EAP team in CAR.

Electronic data will be held only on the RedCap database accessible to specified, individual users with unique logins who are involved in data collection, monitoring and analysis under this protocol.

### Plans for collection, laboratory evaluation and storage of biological specimens for genetic or molecular analysis in this trial/future use {33}

There are no plans to conduct genetic or molecular analysis on biological samples collected from patients enrolled in this EAP.

Patients can however consent to the use of their biological samples for future research. Consent to future use of biological samples is optional. Future research undertaken on these samples will undergo relevant reviews by national ethics committees and/or institutional review boards before any further analyses are undertaken.

## Statistical methods

### Statistical methods for analysing outcomes {20a}

Clinical and virological outcomes will be assessed at D14 and D28 for all patients and then at D21 for patients who are still positive at D14. Due to the non-comparative nature of the study and small number of patients anticipated to be enrolled in the study, only descriptive analyses of clinical and virological outcomes will be presented in the final analysis; no inferential statistical testing will be performed to evaluate changes in outcomes.

To describe the cohort, patient demographics will be described in terms of the ratio of males to females in the cohort, and the median age and range in years. The number and percentage of patients with comorbidities at inclusion, including malaria and human immunodeficiency virus, infection will be presented, along with the median interval in days from symptom onset to initiation of treatment.

Signs and symptoms will be reported in terms of the number and percentage of patients presenting with the symptom, which are assessed at each visit and will be reported at baseline and post-baseline timepoint. Signs and symptoms will be reported for all patients both from a pre-defined list included in the CRF and any additional AEs that may have arisen from the point of consent until D28. The signs and symptom reporting will also include the number and percentage of patients with lesions–subcategorised in to active lesions, crusts and resolved lesions–their distribution and number of lesions observed.

Treatment adherence will be reported in terms of the number and percentage of patients who completed a full course of treatment. Non-adherence will be reported in a supplementary narrative explanation.

Patient outcomes will be reported as the number and percentage of participants who meet the clinical criteria described in Table 3 at D14 and D28, along with the number and percentage of participants who tested positive for mpox virus on D4, D8, D14, D21 and D28.

Narrative summaries of SAEs will be presented alongside a tabulated summary of the number and percentage of patients who experience each SAE, for which event names will be MedDRA coded. For each SAE the grade and outcome will be reported.

Full details of the planned analyses can be found in the Statistical Analysis Plan.

### Interim analysis {21b}

Descriptive analyses of the cohort may be published before the end of the EAP in the interest of communicating information about patient outcomes and the use of tecovirimat for monkeypox which may be pertinent to other research efforts and public health. One such analysis of the first 14 patients enrolled in the EAP was published in September 2022 [15].

### Methods for additional analyses {20b}

All planned analyses on the final dataset will be specified in the Statistical Analysis Plan (SAP).

### Methods in analysis to handle protocol non-adherence and any statistical methods to handle missing data {20c}

The reporting of the study results will consist of descriptive statistics, covering patient demographics, signs and symptoms, clinical outcomes, virological outcomes, and treatment data. Missing data will be clearly reported through the use of denominators or narrative explanations of protocol non-adherence.

### Plans to give access to the full protocol, participant level-data and statistical code {31c}

The full protocol, anonymised participant level-data and statistical code will be either published alongside the study results as supplementary files or available on reasonable request to the programme coordination team.

## Oversight and monitoring

### Composition of the coordinating centre and trial steering committee {5d}

The programme coordinating centre is based at the Institut Pasteur de Bangui with support from the University of Oxford, the study Sponsor. A Programme Management Group oversees day-to-day operational issues relating to the conduct of the programme. The group is formed of members of the coordinating centre and Sponsor and meets at least every two weeks while patients are enrolled during the monkeypox transmission season (September to March). The Programme Management Group is formed of the PIs, co-investigators, laboratory manager, clinical trials manager, and data manager.

A Programme Steering Committee provides overall oversight of the programme and convenes at the beginning and end of the transmission season. The committee is formed of the PIs, co-investigators, clinical trials manager and independent experts in monkeypox.

A medical monitor has been appointed to oversee safety-related aspects of the programme.

### Composition of the data monitoring committee, its role and reporting structure {21a}

As this is not a clinical trial, a data monitoring committee has not been convened. A medical monitor has instead been appointed to oversee issues related to patient safety.

The responsibilities of the medical monitor include, but are no limited to, commenting on any safety considerations related to the protocol, reviewing all Serious Adverse Event (SAE) reports and provide a causality assessment of the relationship between the event and tecovirimat, to periodically review a line listing of all AEs reported, to review all major protocol deviations, and provide advice on their management.

### Adverse event reporting and harms {22}

Details of Adverse Events (AEs) and Serious Adverse Events (SAEs) are collected from the point of consent until the Day 28 visit.

AEs and SAEs are defined and reported according to the WHO Collaborative Centre definitions incorporated in to the European Medicines Agency Guideline for Good Clinical Practice E6 [16].

AEs are recorded directly on the standardised paper CRF and transferred on to the RedCap database by the data manager. The data collected for all AEs includes the event name, event grade, start and end dates and outcome.

SAEs require expedited reporting to the Sponsor. SAEs are defined as any untoward medical occurrence that:

results in deathis life-threateningrequires inpatient hospitalisation or prolongation of existing hospitalisationresults in persistent or significant disability/incapacityconsists of a congenital anomaly or birth defect.

Other ‘important medical events’ may also be considered a serious adverse event when, based upon appropriate medical judgement, the event may jeopardise the participant and may require medical or surgical intervention to prevent one of the outcomes listed above.

All SAEs should be reported to the Sponsor and PI on the standardised SAE report form within 24 hours of the site-based programme team becoming aware of the event.

The treating clinician (the PI or Co-I) will provide a causality assessment of the relationship between the event and tecovirimat. The relationship will be evaluated as either: 1) definitely related; 2) probably related; 3) possibly related; 4) unlikely to be related; 5) not related. The Medical Monitor will provide a second causality assessment using the same scale. Events will be considered as “related” to tecovirimat if either causality assessment is returned as “definitely”, “probably”, or “possibly” related. These events will be considered as Serious Adverse Reactions (SARs). Events that are considered to be “unlikely” or “not related” will remain as SAEs.

The Medical Monitor will also assess the expectedness of the event against the Investigator’s Brochure (IB). Related events that are unexpected will be considered SUSARs.

All SAEs must be reported to the ethics committee of the University of Bangui within 72h of the programme team becoming aware of the event.

All SARs must be reported to the Oxford Tropical Medicine Ethics Committee (OxTREC) within 7 working days.

All AEs and SAEs event terms will be coded according to the Medical Dictionary for Regulatory Activities (MedDRA) terminology.

